### Variables in study

Data collection for the controlled community sample will be done for both arms of the trial on three different moments: before the intervention (at baseline), immediately after its ending and three months later.

The indicators for the intervention effectiveness will be: mental health literacy, mental health related personal and perceived stigma, psychological well-being (depression and anxiety), satisfaction with life and resilience. Secondary outcomes include opinions and satisfaction with intervention by intervened unemployed, rate of participation and completion of the intervention. The socio-demographic variables that will be used to characterize the sample and for adjusting outcomes assessment include: age, gender, educational level, previous professional activities, having or not dependent relatives (children, dependent elderly or other relatives to care) and household overall financial comfort.

All questionnaires measuring/assessing constructs (i.e., latent variables) were selected on basis of their psychometric qualities (e.g., internal and temporal reliability, validity) when applied to adult Portuguese general populations. Table 1 provides an overview of the validated instruments that will be included in the effectiveness assessment. Taking into consideration the time usually reported for filling in each of the selected instruments, it is estimated that the total time for filling the complete battery of questionnaires is around 20 min. We will run a pilot test with at least 10 unemployed persons to assess the burden of the questionnaires.

**Table 1 Tab1:** Instruments used in the effectiveness assessment

Assessed constructs	Questionnaire / measure scale	Description
Mental health literacy	Modified/shortened versions of the following instruments:	The DSS is designed to measure stigma associated with depression. It has two subscales which measure two different types of stigma: personal and perceived. Responses to each item are measured on a five-point scale (ranging from zero ‘strongly disagree’ to four ‘strongly agree’). Higher scores indicate higher levels of depression stigma.
	• Depression Stigma Scale (DSS)	
	• Depression Literacy Questionnaire (D-Lit)	
		The D-Lit assesses mental health literacy specific to depression. The questionnaire consists of 22 items which are true or false. Respondents can answer each item with one of three options – true, false or don’t know. Each correct response receives one point. Higher scores indicate higher mental health literacy of depression.
	• Anxiety Literacy Questionnaire (A-Lit) [46]	
		The A-Lit assesses mental health literacy specific to anxiety. The questionnaire consists of 22 items which are true or false. Respondents can answer each item with one of three options – true, false or don’t know. Higher scores indicate higher mental health literacy of anxiety.
		For each of these scales, we will use the items that will be most adequate to assess literacy gains, according to the contents that will be worked out during the intervention.
Psychological well-being (depression and anxiety)	General Health Questionnaire (GHQ) [47, 48]	The General Health Questionnaire (GHQ) is a screening scale for identifying minor psychiatric disorders in the general population and within community or non-psychiatric clinical settings. GHQ assesses the respondent’s current state and asks if that differs from his or her usual state.
	Brief Symptom Inventory (BSI) [49]	The Brief Symptom Inventory is a 53-item self-report inventory in which participants rate the extent to which they have been bothered (0 = “not at all” to 4 = “extremely”) in the past week by various symptoms. The BSI has nine subscales designed to assess individual symptom groups: somatization, obsessive-compulsive, interpersonal sensitivity, depression, anxiety, hostility, phobic anxiety, paranoid ideation, and psychoticism. The BSI also includes three scales that capture global psychological distress.
Satisfaction with life	Satisfaction with Life Scale (SWLS) [50]	The SWLS is a short 5-item instrument designed to measure global cognitive judgments of satisfaction with one’s life.
Resilience	Connor-Davidson Resilience Scale (CD-RISC) [51]	The CD-RISC is a 25 item scale created to address aspects of resilience and for use in clinical practice.

### Data analysis

Statistical analysis will be carried out using IBM/SPSS 21.0 (or a more updated version, at the moment of the analysis) and R packages. For all tests, the level of statistical significance will be set as α = .05.

For the effectiveness assessment, socio-demographic and outcome variables will be described for each moment of observation. Two strategies of data analysis will be done: (1) intention-to-treat (ITT), as a primary analysis, and; (2) per-protocol, as a supportive analysis. The ITT analysis (treatment as assigned approach), will consider all participants randomly allocated to each arm of the study at baseline with a last observation carried forward imputation for those who did not undergo the final evaluation. The per-protocol analysis (treatment as received approach), will include only the subset of the ITT sample who will completed the evaluations without any major protocol violations. When describing differences between intervention and control group, results from both types of analysis will be reported; for effect size assessment, only per-protocol approach results will be reported, in order to have an estimation of the impact of the treatment as received.

Univariate description of variables will be summarized by central tendency measures (means and medians, according to the normality of their distributions) and respective dispersion measures (standard deviation and range). Normality of data will be assessed through the analysis of kurtosis and skewness.

Association between nominal variables will be assessed through chi-square test (with Yates adjustment, when necessary). Continued variables will be compared (between arms, at the same momentum) by independent samples t-student test or by its non-parametric equivalent (Mann-Whitney test), when adequate.

Effect of the intervention will be studied by linear or logistic regression analysis (according to the nature of the dependent variable), having as dependent variables test-retest variations and adjusting for conceptually (and statistically) relevant variables. Model assumptions will be tested by analysis of residuals and influence diagnostics through Cook’s distance. Cohen’s d coefficient and odds ratio will be used for assessing the size of the intervention effect, when significant.

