**Methods:**

The project follows a RE-AIM-based (Reach, Effectiveness, Adoption, Implementation and Maintenance) framework for assessing a cognitive-behavioural and psychoeducational intervention that has been developed for promoting mental health among unemployed people. It is a short-term group intervention (five sessions, four hours each, 20 unemployed persons per group) focused on mental health literacy, interpersonal communication and of emotional regulation. Implementation of the intervention will be carried out by clinical psychologists, following a standardized procedure manual. Effectiveness will be assessed through a randomized field study with two arms (intervention and control). Participants are unemployed people (18–65 years old, both genders, having at least nine years of formal education) registered at public employment centres from different geographical regions for less than 12 months (including first-job seekers). Allocation to arms of the study will follow a random match-to-case process, considering gender, age groups and educational level. Three moments of evaluation will occur: before intervention (baseline), immediately after its ending and three months later. Main outcomes are mental health literacy, mental health related personal and perceived stigma, psychological well-being, satisfaction with life and resilience. Intention-to-treat and per-protocol analyses will be conducted. Cohen’s d coefficient and odds ratio will be used for assessing the size of the intervention effect, when significant.

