### Aims and objectives

The main goal of this study is to implement a community-based intervention for psychological well-being protection and promotion and to assess its short-term effectiveness. Specific objectives are:(i)to implement a standardized intervention for psychological well-being promotion among Portuguese facing unemployment in two different community settings (rural versus urban settings)(ii)to assess the effectiveness of this mental health promotion intervention in terms of psychological well-being and resilience in job-searching.

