### Sampling aspects

The target population of the HE intervention are unemployed people registered at public employment centres for less than 12 months (including first-job seekers). Random recruitment of participants (for both arms of the study) occurs in two employment centres (from different geographical regions), with match-to-case allocation in arms according to gender, age groups (18–24, 25–44, and 45–65 years old) and educational level (9 to 12, and more than 12 years of completed school – higher education). The full list of the two public employment centres users (with inclusion criteria) will be stratified by gender, age groups and educational level. In each combined stratum, random allocation will be done to each participant who accepts to participate.

Inclusion criteria: unemployed users from public employment centres, 18 to 65 years old, both genders, having at least nine years of formal/public education and being registered in the selected public employment centres at the moment of recruitment.

Exclusion criteria: public employment centres’ unemployed users already attending, at the moment of the recruitment, other public employment centre’s courses, or users with a diagnosed mental or physical severe or incapacitating disease or disability.

Two public employment centres/delegations from two Portuguese regions will be selected (intentional sampling) and invited to participate in the project. The involved public employment centres/delegations differ in terms of size (big dimension vs. small dimension) and type of region (rural population vs. urban population). In each centre/delegation, participants are randomly selected from the full database of users. Allocation to arms is done also in a random way, though following gender, age and educational level strata inter-arms matching.

In each of these settings, the initial (at baseline) users sample size will be of 50 participants with 50 other participants as controls. Previewing a dropout rate of 30% till the end of the project, we estimate to have a final users’ sample size of 35 participants in each of the arms, in each employment centre (70 participants per arm, in total). With this sample size, we expect to have 80% power to detect an effect size of 0,48 in mean scores of mental health literacy, psychological well-being, satisfaction with life and resilience [45].

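### No primary outcome or time point is named: at least eight scores at two follow-ups are each tested at .05, while the stated power covers a single test

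*Protocol article*

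**What the plan says.** The Abstract states: "Main outcomes are mental health literacy, mental health related personal and perceived stigma, psychological well-being, satisfaction with life and resilience". Variables in study repeats the same five constructs, opening with "The indicators for the intervention effectiveness will be: mental health literacy, mental health related personal and perceived stigma". That section keeps the word secondary for satisfaction with the intervention, participation and completion, so the five constructs stand together at the top. None is ranked above another.

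Table 1 attaches instruments to them: the Depression Stigma Scale (DSS) with a personal and a perceived subscale, the depression and anxiety literacy questionnaires (D-Lit, A-Lit), the GHQ, the BSI, the SWLS and the CD-RISC. Of the BSI it says "The BSI has nine subscales designed to assess individual symptom groups", adds three global scales, and does not select any. Assessments follow baseline twice: directly after the intervention and three months later.

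Two other places use shorter lists. Aims and objectives frames effectiveness "in terms of psychological well-being and resilience in job-searching". Sampling aspects claims 80% power at an effect size of 0.48 "in mean scores of mental health literacy, psychological well-being, satisfaction with life and resilience".

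On error control, Data analysis says: "For all tests, the level of statistical significance will be set as" α = .05. It calls intention-to-treat the primary analysis, which picks an analysis set but not an outcome or a visit.

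**The concern.** With five equal outcomes, eight or more scores and two visits, the plan does not say which result answers the effectiveness question. Each comparison has its own 5% error rate, and nothing limits the error across them.

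Consequences hang on the answer. Ethics offers the intervention to controls if it turns out effective. The Discussion ties new funding applications to positive results at the last observation. Neither passage says on which score this is judged. Data analysis also plans to report effect sizes only for significant effects, so chance positives are the ones that would be given an effect size.

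The power statement has the matching problem: it is worded for four constructs at once, while the calculation behind it fits one test.

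**Working it through.** **Inputs from the protocol article**
- Level: .05 for every test (Data analysis). Sidedness is not stated; the plan names "independent samples t-student test or by its non-parametric equivalent (Mann-Whitney test), when adequate" for comparisons between arms.
- Sample: 50 per arm in each of two centres, so 100 per arm; 30% dropout leaves 100 × 0.7 = 70 per arm (Sampling aspects).
- Scores (Table 1): DSS personal, DSS perceived, D-Lit, A-Lit, GHQ, at least one BSI score, SWLS, CD-RISC = at least 8.
- Follow-ups: 2 (Variables in study), so at least 16 score-by-visit tests.

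**Assumptions (not in the article)**
- Correlation among scores: 0 to 0.7. Correlation of one score between the two follow-ups: 0.5 to 0.7. Correlation of different scores at different visits: the product of the two.
- Any one significant score counts as effectiveness.

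**Step 1. Reproduce the stated power.** The expected z is 0.48 × √(70/2) = 2.84. Two-sided at .05, power = Φ(2.84 − 1.96) = 81.1%; the noncentral t gives 80.5%, and 80% power needs 69.1 per arm. A one-sided .05 test would give 88.4%. The stated figure therefore fits one two-sided test at .05, and two-sided testing is used below.

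**Step 2. Independent tests, no true effect.**
- Either direction: 1 − 0.95^8 = 33.7%; 1 − 0.95^16 = 56.0%.
- Favouring the intervention (.05/2 = .025 per test): 1 − 0.975^8 = 18.3%; 1 − 0.975^16 = 33.3%.

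**Step 3. Correlated tests.** Multivariate normal simulation, 400,000 draws per setting, critical value 1.96. Cells with two figures are for between-visit correlations of 0.5 / 0.7.

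| Correlation among scores | 8 scores, 1 follow-up: either direction | favouring | 8 scores, 2 follow-ups: either direction | favouring |
|---|---|---|---|---|
| 0 | 33.6% | 18.3% | 53.2 / 50.3% | 31.0 / 29.0% |
| 0.3 | 30.0% | 15.1% | 48.2 / 45.2% | 25.3 / 23.4% |
| 0.5 | 25.0% | 12.6% | 41.3 / 38.5% | 21.1 / 19.3% |
| 0.7 | 19.0% | 9.6% | 32.2 / 29.8% | 16.2 / 14.9% |

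As a lower bound on the count, five scores (one per construct) at one follow-up give 14.8–22.6% in either direction and 7.4–11.9% in favour.

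**Step 4. Cost of adjusting instead of choosing.** With Bonferroni over 8 scores (.00625 each), power at 0.48 with 70 per arm falls to 52.7%. Reaching 80% would need 113 evaluable per arm, or 113/0.7 = 161.4, so 162 enrolled per arm against the planned 100. One named score at one visit keeps 5% error and 80.5% power with the planned sample.

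**Step 5. Compare the outcome lists.** The Abstract and Variables in study agree on five constructs. Sampling aspects gives four, without stigma. Aims and objectives gives two.

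**The case against.** A separate analysis plan may exist and could rank the outcomes; a fixed testing order can even keep each test at .05. That possibility stands. But the article itself labels five constructs as main, reserves secondary for process measures, and states its level for all tests, so any such ranking would add something that the article's own wording does not suggest.

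Several stronger readings are tempting and are not supported:

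- *That the risk of a false claim of effectiveness is 25–55%.* Figures of that size count differences in either direction, including those favouring control. A false claim of benefit needs a favourable result, which roughly halves the risk.
- *That the top value of 56% is realistic.* It needs the same score in the same people to be uncorrelated across visits. Carrying the last observation forward, with 30% dropout expected, pushes that correlation up.
- *That the plan says one significant test is enough.* It sets a significance level and no success rule; the any-one-score criterion is an assumption made to size the problem.
- *That three sections list different main outcomes.* Only the Abstract uses that label, and Variables in study matches it. Table 1 places the stigma scale under mental health literacy, so its absence from the power statement may be only a matter of grouping. The clear mismatch is the narrower pair in the objective.
- *That all twelve BSI scales will be tested.* Table 1 describes the instrument, and Variables in study narrows well-being to depression and anxiety.

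The Discussion also calls the three-month visit the final evaluation and refers to results at the last observation. This points to three months and makes the one-follow-up figures the relevant ones for that decision, but it does not formally name a primary time point. Ethics gives no time point at all.

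**Conclusion.** The point holds. The plan ranks none of five main outcomes, leaves at least eight scores and two visits open, tests everything at .05, and states a power that is valid for one test only.

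With no true effect, and with any one significant score taken as effectiveness, the chance of at least one result favouring the intervention is about 9.6–18% for eight scores at one follow-up and 15–31% at two, against a nominal 2.5%: roughly 4 to 12 times (9.6/2.5 = 3.8; 31.0/2.5 = 12.4). For a difference in either direction the figures are about 19–34% and 30–53%, against 5%. Full independence would bring the two-follow-up values to 33% and 56%.

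The ranges rest on assumed correlations and on the assumed success criterion. The structural defect, an effectiveness question with no designated answer, depends on neither.

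**What to change.** Before outcomes are compared by arm:

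- Name one primary score and one time point that match the stated main goal, for example one psychological well-being score at the three-month final evaluation. The sponsor chooses the score. Test it two-sided at .05.
- Define the effectiveness condition in Ethics and the positive results in the Discussion on that test.
- Make the other scores and the immediate post-intervention assessment secondary, with Holm adjustment. Treat BSI scales that are not selected as exploratory.
- Align the Abstract, Aims and objectives, Sampling aspects and Variables in study, and state that the 80% power applies to the one primary outcome.

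This costs wording only and needs no additional participants. The downside is that claims on secondary outcomes become harder to make.

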## Discussion

In a context of adverse economic climate, vulnerable groups experiencing unemployment have an increased risk of suffering from mood disorders and psychological distress [5, 53, 54]. This paper describes a community-based randomized field study protocol for assessing the effectiveness of a psychological well-being protection and promotion intervention, aiming to build capacity and reduce inequalities within the context of unemployment. This intervention is foreseen as strategic due to its applicability to different community settings and targeted populations. Moreover, the intervention has also a component of socio-cognitive skills development and training for an adequate recognition of psychological suffering and referral to primary healthcare and mental health services.

A main challenge of the field experiment concerns some fundamental characteristics of the intervention, namely in terms of format and duration. The intervention is currently planned to follow a short-term group format, maximizing its potential to be adopted, replicated and sustained in different settings (in both public and private sectors). Another difficulty relates to the fact that the population that may benefit from the intervention is highly heterogeneous, namely regarding financial, sociocultural backgrounds and level of psychological suffering. Therefore, the added-value of the intervention for participants will vary substantially and the overall trial results will need to be stratified by individuals’ characteristics.

Considering the timeframe of the EEA Grants 2009–2014 that financially supported this project (see acknowledgements/funding section), the final evaluation of the intervention will be done three months after its ending. This is a limitation of this study protocol because three months might be a narrow time frame for detecting mental health promotion effects and, on the other hand, possible intervention-related changes can be temporary and not sustainable. Nevertheless, if the intervention shows positive results at the last observation moment, the project team will apply for new funding opportunities to follow the recruited cohort (within this trial) for a longer period.

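### Last observation carried forward in the primary ITT analysis can bias the three-month difference in either direction, with 30% dropout expected

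*Protocol article*

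**What the plan says.** The Data analysis section names two strategies: "1) intention-to-treat (ITT), as a primary analysis, and; (2) per-protocol, as a supportive analysis". The ITT set is everyone randomised, "with a last observation carried forward imputation for those who did not undergo the final evaluation". The per-protocol set "will include only the subset of the ITT sample who will completed the evaluations without any major protocol violations". No other treatment of missing outcomes is given. Between-arm differences are to be reported from both analyses, but effect sizes from the per-protocol set only. The intervention effect is modelled by regression on change between assessments.

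Variables in study sets three assessments: baseline, straight after the programme, and three months later.

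Sampling aspects gives the numbers. In each of two centres, "the initial (at baseline) users sample size will be of 50 participants with 50 other participants as controls". Then: "Previewing a dropout rate of 30% till the end of the project", leaving "a final users’ sample size of 35 participants in each of the arms, in each employment centre (70 participants per arm, in total", with "80% power to detect an effect size of 0,48 in mean scores of mental health literacy" and the other listed outcomes.

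The Discussion, on the limits of a three-month horizon, notes that "possible intervention-related changes can be temporary and not sustainable".

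**The concern.** With three assessments, a participant who misses the last one can contribute only one of two carried values. Someone who left after the post-test contributes that score, so a gain seen on the last day of the programme counts as a gain at three months. Someone who left before the post-test contributes the baseline score, which records no change. Each substitution holds only if nothing moves after the last visit. The protocol gives no ground for assuming that, and its own remark about temporary changes sits badly with it.

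The three-month visit is the final evaluation, and the Discussion ties a bid for longer follow-up funding to a positive result there. A rule that can turn an immediate effect into an apparent lasting one, or dilute a real lasting one, bears directly on that result.

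**Working it through.** **Inputs from the protocol.** 100 per arm at baseline (50 in each of two centres); 30% dropout; 70 per arm at the end; design effect 0.48 SD; power 80%; α = 0.05. Sidedness is not stated; two-sided is taken because it reproduces the stated power.

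**The protocol's own figure.** A two-sample t-test with 70 per arm and effect 0.48 has power 80.5% (81.1% by normal approximation; one-sided would be 88.4%). Inflation for dropout is 70/(1 − 0.30) = 100 per arm. Both figures reproduce.

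**How much is filled in.** 0.30 × 100 = 30 per arm, or 60 of 200 three-month values.

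**Expected LOCF difference.** Let d1 be the effect straight after the programme, d2 the true three-month effect, and q the share of dropouts who have a post-test score (the rest carry baseline, where the arms do not differ on average). With dropout completely at random and equal between arms:

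E = 0.70 × d2 + 0.30 × q × d1

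The values of d1, d2 and q are assumptions; the protocol gives none. With d1 = 0.48:

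| True d2 | q = 1 | q = 0.5 | q = 0 |
|---|---|---|---|
| 0 | 0.144 | 0.072 | 0 |
| 0.24 | 0.312 | 0.240 | 0.168 |
| 0.48 | 0.480 | 0.408 | 0.336 |

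Examples: 0.70 × 0 + 0.30 × 0.48 = 0.144; 0.70 × 0.24 + 0.30 × 0.48 = 0.312 (+30%); 0.70 × 0.48 + 0 = 0.336 (−30%).

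**Rejection rate when the three-month effect is truly zero (d1 = 0.48, q = 1).** For change scores with correlation ρ between visits, the variance is 2(1 − ρ). The intervention arm adds 0.3 × 0.7 × 0.48² = 0.048 because it mixes two means, so the average over arms is 2(1 − ρ) + 0.024.

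- ρ = 0.5: SD = √1.024 = 1.012; standardised effect 0.144/1.012 = 0.142; times √50 gives 1.01; rejection about 17%.
- ρ = 0.6: SD = √0.824 = 0.908; 0.144/0.908 = 0.159; times √50 gives 1.12; rejection about 20%.

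A simulation at ρ = 0.6 (100 per arm, 4,000 runs) gave a mean estimate of 0.144 with 19.9% rejection. With q = 0.5 it gave 0.074 with 9.6%. Completers in the same runs gave estimates near 0 with 5.6% and 5.4% rejection. The excess therefore comes from the filled values.

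**Standard errors.** In simulation at ρ = 0.6 with equal random dropout, the mean model standard error and the actual sampling SD of the LOCF change-score estimate were 0.126 and 0.127 (q = 1), 0.117 and 0.116 (q = 0.5), and 0.106 and 0.106 (q = 0). With no effect at either visit, rejection was 4.8–5.1%.

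**Power in the worst dilution case (d2 = 0.48, q = 0).** On final scores, an effect of 0.336 with 100 per arm has 66% power. On change scores at ρ = 0.5, the variance is 0.70 × 1 + 0.024 = 0.724, SD 0.851, standardised effect 0.336/0.851 = 0.395, power 79%. At ρ = 0.6, simulated power is 88%.

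**The case against.** The case on the other side has several parts.

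- **Contradiction.** A reader might infer that the protocol contradicts itself by using LOCF while expecting effects to fade. It does not. The Discussion names a possibility, in a sentence about the short horizon, and can be read as meaning fading after three months, which LOCF up to that visit does not touch. What stands is weaker: the rule needs scores to stay constant after the last visit, and the protocol voices doubt about durability.
- **Standard errors.** Single imputation is often said to understate them. Under equal random dropout they match the sampling SD here, and rejection is nominal when there is no effect at either visit. The harm is in the mean difference.
- **Power and sample size.** Sizing on 70 completers is ordinary dropout inflation, and the stated power reproduces. The 66% figure belongs to a final-score comparison. For the planned change-score model, power stays at about 79–88% even in the worst dilution case, so no sample-size error follows.
- **Reach.** Effect sizes come from the per-protocol set, so the inflated 0.14 or 0.31 would not be the published effect size. This stands. LOCF acts on the primary ITT differences and tests.
- **Extremes.** The largest biases need all dropouts to leave on the same side of the post-test. With an even split and an effect that halves to 0.24, the LOCF estimate is exactly 0.24. This also stands. But the timing is unknown in advance, so agreement would be luck.

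The per-protocol analysis does not repair the problem. It drops the dropouts' post-test scores, excludes major violators and does not preserve the randomised comparison.

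**Conclusion.** The point holds as a bias in a stated primary-analysis rule. With 30% dropout, LOCF can move the three-month between-arm difference by up to 0.144 SD in either direction in these scenarios, against a design effect of 0.48. If an immediate effect of 0.48 has vanished and all dropouts carry the post-test, the false-positive rate is about 17–20% rather than 5%. This rests on assumed values for the fading pattern, dropout timing and between-visit correlation (0.5–0.6), and on equal random dropout. Intermediate timing gives smaller or no bias. At most the three-month values are affected to the extent of 30%; the protocol names no single primary time point. An internal contradiction, understated standard errors or an incorrect sample size should not be inferred. This should be fixed, but it does not undermine the design.

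**What to change.** In the Data analysis section, replace LOCF in the primary ITT analysis with one of two methods:

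- a likelihood-based repeated-measures mixed model on all observed post-test and three-month scores, with baseline as covariate, an arm-by-time term, centre and the stratification factors; or
- multiple imputation using arm, baseline, post-test and strata.

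Both are valid under missing at random and use the post-test score without assuming that it persists. Keep LOCF at most as a sensitivity analysis, ideally beside one delta-adjusted analysis for data missing not at random.

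The cost is a change of wording and slightly more analysis work. R and SPSS, already named, can do it, and no new data are needed. The downside is reliance on missing at random, which the data cannot confirm; the delta-adjusted analysis shows how far the result depends on it.
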